### Interventions

Patients in the three intervention groups will be given ten rounds of electroacupuncture stimulation on corresponding acupoints for 2 weeks, five times per week, with 2 days of rest between the two treatment courses. Patients in the insomnia control group will also receive the same two courses comprising ten rounds of compensatory acupuncture therapy after the 2-week waiting period for treatment. The healthy control group will not be given any intervention.

#### Selection of the acupoints

EA-SM group: HT 7, auxiliary acupuncture point 1EA-SY group: SP 6, auxiliary acupuncture point 2EA-SS group: HT 7, SP 6, auxiliary acupuncture point 1, auxiliary acupuncture point 2

All the acupoints above are selected symmetrically on the left and right sides of the limbs.

#### Location of the acupoints

According to the National Standards of the People’s Republic of China: Name and Location of Acupoints (*GB/T 12346-2006*) to locate HT 7 and SP 6, auxiliary acupuncture point 1 and point 2 are selected according to the following references [23]:
HT 7: on the ulnar side of the distal volar wrist stripes and the radial margin of the flexor carpi ulnaris tendon in the anterior wrist areaSP 6: 3 *cun* straight up to the tip of medial malleolus, posterior border of medial tibia, on the inner side of the calfAuxiliary point 1: located at 2 mm above HT 7Auxiliary point 2: located at 2 mm above SP 6 Locations of HT 7, SP 6, auxiliary point 1 and 2 are as shown in the Fig. 3.

**Fig. 3 Fig3:**
[figure not shown]
Locations of HT 7, SP 6 and auxiliary acupuncture points on one side of the body, with the same position on the other side symmetrically. Red point: HT 7; Blue piont: auxiliary acupuncture point 1; Green point: SP 6; Yellow point: auxiliary acupuncture point 2. The auxiliary acupuncture point 1 and 2 are 2mm above HT 7 and SP 6. Red and blue points are the acupoints used for EA-SM group. Green and yellow circles are the acupoints used for EA-SY group; the all circles are the acupoints used for EA-SS group

#### Therapeutic procedures

Electroacupuncture will be performed by trained acupuncture operators. A sterile acupuncture needle will be inserted into HT 7 at a depth of 0.3 to 0.5 *cun* (length 25 mm, diameter 0.25 mm; Huatuo, Suzhou Medical Supply Factory Co. Ltd., Suzhou, China), into SP 6 at a depth of 0.5 to 1 *cun* (length 40 mm, diameter 0.25 mm; Huatuo, Suzhou Medical Supply Factory Co. Ltd., Suzhou, China) with the de qi sensation (a compositional sensation including soreness, numbness, distention, and heaviness), and into the auxiliary points to a depth of 0.2 *cun* (length 13 mm, diameter 0.18 mm; Huatuo, Suzhou Medical Supply Factory Co. Ltd., Suzhou, China) without the de qi sensation. Then the operators will apply electroacupuncture stimulation (SDZ-II electroacupuncture therapy apparatus; Huatuo, Suzhou Medical Supply Factory Co. Ltd., Suzhou, China) by connecting HT 7 and the auxiliary point 1 as one pair of electrodes and connecting SP 6 and the auxiliary point 2 as another, using density-wave electrical stimulation with a frequency of 5 Hz to 25 Hz and current intensity between 1.0 mA and 1.5 mA. The output strength of electroacupuncture will be set according to the maximum tolerated intensity and the comfort feeling of each subject. The treatments will last 30 min. They will be given ten times for 2 weeks, five times per week, with 2 days of rest between the two treatment courses.

The subjects in the three intervention groups will be prohibited from receiving any other relevant treatment during the trial period. In our study, no drug combination that can improve sleep is permissible. All relevant treatments and medication compliance will be recorded in the case report form.

## Outcome measures

### Major outcome measures

The major outcome measure in this study is the SDRS, which is a quantitative assessment tool for insomnia severity based on the Chinese classification and diagnostic criteria for mental disorders (third edition), with good reliability and validity for assessing sleep quality, sleep duration, different clinical manifestations of insomnia, and the discomfort associated with insomnia [24].

### Secondary outcome measures

Secondary outcome measures of this study include the Insomnia Severity Index (ISI), the Epworth Sleepiness Scale (ESS), the Zung Self-Rating Anxiety Scale (SAS), and the Zung Self-Rating Depression Scale (SDS) to evaluate the insomnia and emotional state of patients with insomnia; the Measure Your Medical Outcome Profile to evaluate the main symptoms of the patients according to self-report; the Sleep Latency(SL), Total Sleep Time(TST), and so forth collected through polysomnography (PSG); and the quantity of acetylcholine (Ach), serotonin (5-HT), dopamine (DA), norepinephrine (NE), melatonin (MT), gamma-aminobutyric acid (GABA), and metabolic biomarkers in serum. By these measures, we hope to explore the acupoint combination effect of HT 7 and SP 6 in treating insomnia and its neurobiological and metabolic mechanisms.

## Data analysis

Statistical analysis includes the actual number of subjects, cases of shedding and exclusion, demographic and other baseline characteristics, compliance analysis, safety assessment, insomnia and emotional state scores, SL, TST, and quantity analysis of serum neurotransmitters and hormones. IBM SPSS Statistics for Windows version 19.0 software (IBM Corp., Armonk, NY, USA) will be used for statistical analysis. We will adopt univariate analysis of variance to analyze the age, height, weight, scale score, SL, TST, neurotransmitter and hormone content, and so forth, and we will use the chi-square test to analyze gender comparison and the rank-sum test to analyze the course of disease. *P* < 0.05 will be considered as the standard of statistical significance. Serum will be analyzed by liquid chromatography–mass spectrometry, and the serum metabolic biomarkers of insomnia will be screened using MetaX metabolomic data analysis software (BGI Genomics Co. Ltd., Shenzhen, China).

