### Sample size

This study sample size is calculated on the basis of a ratio of 1:1:1:1 between the intervention groups and the control group. Though there are four study groups, the study can be regarded as a comparison between each intervention group and the control group. This study refers to the method of sample size estimation in this paper [20]. In those studies, the sample sizes are based on studies that investigated the effect of acupuncture-related treatment on insomnia using the Sleep Dysfunction Rating Scale (SDRS) as a major outcome [21, 22], and the number of participants required for each group is 30 or 31. In addition, in the study [21], the mean change in SDRS between the intervention and control groups was 2.69, and the standard deviation was estimated from the means and the standard deviations of intervention (− 14.80 ± 3.52) and control groups (− 12.11 ± 2.38). On the basis of a two-tailed alpha error of 5% and with a statistical power of 90%, the calculated sample size is based on the equation:
$$ N=\frac{2\times {\left(\frac{Z\alpha}{2}+ Z\beta \right)}^2\times {\sigma}^2}{\delta^2} $$$$ N=\frac{2\times {\left(1.96+1.28\right)}^2\times {3.00}^2}{2.69^2}=26.11 $$

Therefore, this study’s sample size is 120, assuming a 15% dropout rate, and all 120 participants will be randomly assigned, with 30 subjects in each group.

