Metabolomics, guided by the theory of system biology, monitors the changes of endogenous metabolites of organisms and directly reflects the body’s response to external pathophysiological stimulation and intervention from the perspective of the whole system. It depends on spectral research and pattern recognition methods with high throughput, high sensitivity, and high accuracy. We hypothesize that the tranquilizing effect (which means the effect to improve sleep) produced by acupoint combination may be the overall effect of the integrated action of multiple links, channels, and targets in the human body. Metabolomics emphasizes the study of human beings as a complete system, coinciding with the whole view of TCM acupuncture theory. This technique has also been used to carry out research on insomnia. A study explored the mechanism of SuanZaoRen (*Ziziphi spinosae semen*) decoction to improve the sleep of rats with insomnia, screened 11 potential biomarkers related to insomnia, and obtained 8 potential metabolic pathways [27] based on ^1^H nuclear magnetic resonance metabolomics. Another study analyzed the changes of brain metabolism in mice after injection of ginseng glycoproteins by metabolomics [28]. Therefore, this study will adopt the metabolomic research method to compare the changes of endogenous metabolites before and after acupuncture intervention in different groups to find the differences in their metabolic profiles and possible related metabolic pathways, and these differential metabolic markers may be associated with insomnia. We will observe the internal mechanism of acupoint combination efficacy from a holistic, systematic, and comprehensive perspective. This can provide ideas and evidence for exploring the mechanism of acupuncture therapy on insomnia.

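### Scale scores are to be compared by ANOVA with no baseline term and no statement of whether the score is post-treatment or change; baseline-adjusted ANCOVA would be at least as precise on either reading and costs almost nothing

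*Protocol article*

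**What the plan says.** The Major outcome measures section names one instrument: "The major outcome measure in this study is the SDRS". The Data analysis section gives one method for all continuous variables, demographic and outcome alike: "We will adopt univariate analysis of variance to analyze the age, height, weight, scale score, SL, TST, neurotransmitter and hormone content". Neither that section nor any other mentions a baseline covariate, a change score for the scales, or analysis of covariance.

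The Sample size section works on change. It states that "the mean change in SDRS between the intervention and control groups was 2.69" in an earlier study, and that "the standard deviation was estimated from the means and the standard deviations of intervention" and control groups, given as −14.80 ± 3.52 and −12.11 ± 2.38. The error rates are a "two-tailed alpha error of 5% and with a statistical power of 90"%. The powered contrast is pairwise: "the study can be regarded as a comparison between each intervention group and the control group".

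**The concern.** The 90% power belongs to a comparison of mean changes with SD 3.00. The analysis sentence could be carried out on post-treatment scores, which have a different SD, or on changes. Someone following it could do either and be within the plan. If post-treatment scores are used, the planned power need not apply, and a strongly predictive baseline value goes unused. If changes are used, the analysis matches the sizing but is still less precise than adjusting for baseline.

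The design does little else to control baseline severity. Arms have 30 patients, two hospitals recruit, and the Randomization and allocation concealment section describes complete randomisation with no stratification. Chance differences in baseline SDRS between arms are possible, and the named analysis does not adjust for them.

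**Working it through.** **Inputs from the Sample size section.** Difference 2.69; SDs of change 3.52 and 2.38; two-sided alpha 5%; power 90%; 30 per arm; 15% dropout.

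**Step 1: reproduce the plan's figure.**
- Pooled SD = √[(3.52² + 2.38²)/2] = √9.027 = 3.005, used as 3.00.
- N = 2 × (1.96 + 1.28)² × 3.00² / 2.69² = 188.96 / 7.236 = 26.11 per arm, as stated.
- Completers per arm = 30 × 0.85 = 25.5.
- Power on change: 2.69 / [3.00 × √(2/25.5)] = 3.20; 3.20 − 1.96 = 1.24; power 89.3%.

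The sizing is therefore sound for change.

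**Step 2: assumptions not in the documents.** Let rho be the within-arm correlation between baseline and post-treatment SDRS. It is not given, so a range is shown. Baseline and post-treatment SDs are taken as equal, and the change SD is held at 3.00.
- Post-score SD = 3.00 / √[2(1 − rho)]
- ANCOVA residual SD = post-score SD × √(1 − rho²) = 3.00 × √[(1 + rho)/2]

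**Step 3: pairwise power for 2.69 with 25.5 completers per arm (normal approximation).**

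| rho | Post-score SD | Post-score ANOVA | Change-score ANOVA | ANCOVA SD | ANCOVA |
|---|---|---|---|---|---|
| 0.3 | 2.54 | 96.6% | 89.3% | 2.42 | 97.8% |
| 0.5 | 3.00 | 89.3% | 89.3% | 2.60 | 95.9% |
| 0.6 | 3.35 | 81.7% | 89.3% | 2.68 | 94.7% |
| 0.7 | 3.87 | 69.9% | 89.3% | 2.77 | 93.5% |
| 0.8 | 4.74 | 52.6% | 89.3% | 2.85 | 92.1% |

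The same in patients: for 90% power, post-score ANOVA needs 19, 27, 33, 44 and 66 completers per arm at these five values, and ANCOVA needs 17, 20, 21, 23 and 24.

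**Step 4: check with the noncentral t.** Figures fall by one to two points: change-score 88.1%; post-score 80.2% and 68.1% at rho 0.6 and 0.7; ANCOVA 93.9% and 92.5%. At rho 0.9, ANCOVA has 90.7% (normal) or 89.6% (t).

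**Step 5: variance ratios.** ANCOVA variance is (1 − rho²) times that of post-score ANOVA and, with equal SDs, (1 + rho)/2 times that of change-score ANOVA. At rho 0.5 both ratios are 0.75, so 30 patients analysed by ANCOVA carry the information of 30/0.75 = 40 analysed either other way.

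**The case against.** The strongest reply is that the sentence does not commit to post-treatment scores. A reader might infer that analysis and sizing definitely use different quantities. The text does not support that: the scale score may mean change, in which case the mismatch disappears and power is about 89%, essentially as planned. This objection stands. What remains is that the sentence leaves the primary variable open and names no baseline term.

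A reader might also infer that the trial is underpowered as analysed. That needs two things the documents do not give: analysis of post-treatment scores, and rho above about 0.5. Below that value, post-score ANOVA does better than change.

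Nor is change-score analysis biased by regression to the mean. Under randomisation this acts on all arms alike, and both simple analyses are unbiased over repeated randomisations. The gain from ANCOVA is precision and protection against imbalance in the sample actually drawn. Such imbalance is possible; nothing shows it to be likely.

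The Discussion says the authors will "compare the changes of endogenous metabolites before and after acupuncture intervention in different groups". That concerns untargeted metabolites, which the Data analysis section assigns to separate software, so it does not settle how SDRS is handled.

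Finally, a short article may leave covariates to a fuller plan. That would answer a complaint about silence. Here the article names a method for the major outcome, and the method named can be improved on either reading.

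**Conclusion.** The point holds as an ambiguity in the primary analysis together with an inefficient choice of method. It is not a demonstrated error or a proven loss of power. On the post-treatment reading, power runs from about 97% at rho 0.3 to 53% at rho 0.8 and crosses the planned level near rho 0.5. On the change reading it is about 89% throughout. ANCOVA gives about 98% to 92% over the same range and is at least as precise as either alternative, apart from one degree of freedom.

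The figures rest on equal baseline and post-treatment SDs, a change SD of 3.00, 15% dropout and pairwise tests at 5%, as in the Sample size section. The four-group F test is a separate matter. They also assume that SDRS is measured at baseline, since the assessment schedule is in a figure not shown. This should be changed, but the trial does not fail without it.

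**What to change.** Before group data are seen, record in a dated amendment that post-treatment SDRS will be analysed by ANCOVA, with arm as factor and baseline SDRS as covariate. Take each intervention-versus-control difference and its 95% confidence interval from that model. Apply the same model to the other scales, and to polysomnography and serum measures where a baseline value is collected. Adjustment for hospital is optional.

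The cost is a short amendment and one degree of freedom per model. No extra patients or visits are needed if baseline SDRS is already recorded, and the SPSS univariate procedure accepts a covariate. Timing matters: the Trial status section reports 115 of the planned 120 participants recruited and through the intervention, so the amendment must be dated and must precede any look at results by arm.

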## Quality control and guarantee

The researchers are trained before the study, including the research process, implementing rules, criteria for inclusion and exclusion of diagnosis, treatment regimen, acupoint selection and acupuncture operation, curative effect observation, data collection and management, and adverse event reporting and recording. The trial will be terminated under the following conditions: serious adverse events, serious complications, or deterioration of condition, in which case the clinical trial should be stopped according to the judgment of the doctor, or when participants are reluctant to continue the study and ask to drop out, or upon occurrence of special physiological changes (such as pregnancy) during the study period that make it inappropriate to continue. A study coordination and management team is set up to take charge of the management and quality control of the test program and supervise the research process, ensuring that the research data recording and reporting are correct, complete, and consistent with the original data. The scale evaluation is completed by particular persons. PSG is conducted by professionals according to professional testing procedures in the Sleep Medicine Center of West China Hospital of Sichuan University. Serum metabolomics are tested and analyzed by BGI Genomics Co. Ltd. Neurotransmitters and hormones are detected in strict accordance with the kit instructions. When the subjects drop out, they will be interviewed face to face, followed up by phone or mail and so forth to ask for reasons, record the time of the last treatment, and complete the evaluation items as far as possible. For patients who withdraw from the study due to adverse reactions, ineffective treatment, or other changes in their conditions, corresponding treatment measures shall be taken according to the actual conditions of the subjects. Patients receiving more than half of the treatment course among those who have been ranked with random numbers will be included in the statistical analysis. All dropouts will be analyzd according to intention-to-treat principle after the trial.

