**Fig. 2 Fig2:**
[figure not shown]
Study schedule of enrollment, interventions, and assessments. The template is derived from the Standard Protocol Items: Recommendations for Interventional Trials (SPIRIT) 2013 statement. The patients in the control group will finish the assessments and then receive compensatory acupuncture therapy at week 3 after the 2-week waiting period (week 1, week 2). *EA-SM Group* electroacupuncture on Shenmen (HT 7), *EA-SY Group* electroacupuncture on Sanyinjiao (SP 6), *EA-SS Group* electroacupuncture on Shenmen (HT 7) and Sanyinjiao (SP 6), *SDRS* Sleep Dysfunction Rating Scale, *ISI* Insomnia Severity Index, *ESS* Epworth Sleepiness Scale, *SAS* Zung Self-Rating Anxiety Scale, *SDS* Zung Self-Rating Depression Scale, *PSG* polysomnography

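### The protocol gives two unlabelled inclusion rules that conflict for early stoppers in the electroacupuncture arms, and the exposure-based rule cannot be applied evenly to the waitlist control

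*Protocol article*

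**What the plan says.** Two consecutive sentences in the protocol article, under Quality control and guarantee, deal with who is analysed. The first reads "Patients receiving more than half of the treatment course among those who have been ranked with random numbers will be included in the statistical analysis". The second reads "All dropouts will be analyzd according to intention-to-treat principle after the trial". Neither is called primary, per-protocol or sensitivity, and the Data analysis section names no analysis set.

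The same section foresees patients who "withdraw from the study due to adverse reactions, ineffective treatment, or other changes in their conditions". It also commits staff to follow up dropouts and "complete the evaluation items as far as possible".

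On exposure, the Interventions section says "Patients in the three intervention groups will be given ten rounds of electroacupuncture stimulation on corresponding acupoints for 2 weeks, five times per week". For the waitlist arm, the Fig. 2 legend says "The patients in the control group will finish the assessments and then receive compensatory acupuncture therapy at week 3 after the 2-week waiting period".

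**The concern.** The primary analysis population should be fixed before anyone sees results. Here an analyst could follow either sentence and claim to have followed the protocol.

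The two rules also differ in quality. Intention to treat keeps the groups that randomisation formed. The more-than-half rule conditions on something that happens after randomisation and may be linked to outcome, since the protocol itself lists lack of effect and adverse reactions among the reasons for withdrawal. It also depends on a treatment course that the control arm has not begun when its outcome is measured. The sample size rests on comparing each EA arm with control, so a rule that acts differently on the two sides bears on the trial's main contrasts.

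**Working it through.** **The plan's own figure.** Sample size section: difference 2.69, SD 3.00, two-sided alpha 5%, power 90%.

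N = 2 × (1.96 + 1.28)² × 3.00² / 2.69² = 188.96 / 7.236 = 26.11 per arm, as stated. The SD agrees with the two arm SDs: √((3.52² + 2.38²)/2) = 3.005. The concern changes nothing here. The 2.69 serves below only as a yardstick.

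**The two rules side by side.** If the course means all ten sessions, more than half means at least six.

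| Randomised patient | More-than-half rule | Intention-to-treat sentence |
|---|---|---|
| EA, 10 sessions | in | in |
| EA, stops after 6 | in | in |
| EA, stops after 4 | not in | in |
| Control at end of week 2, no sessions yet | undefined | in |

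The third row is the direct conflict. The threshold is itself unclear, because the protocol also describes the ten sessions as two courses of five.

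**Applying the exposure rule to controls.** There are three ways, none even-handed:

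- Count only the waiting period: every control fails.
- Count the compensatory course from week 3: controls are selected on attendance after their outcome was assessed.
- Waive the rule for controls: exclusions fall only on the EA arms. This is the most workable option, and the one illustrated next.

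**Illustrative size under the waiver.** Let p be the share of an EA arm excluded and D the amount by which those excluded improve less than those retained. If the retained mean improvement is m, the full-arm mean is (1 − p)m + p(m − D) = m − pD. The retained mean is therefore too favourable by pD. Both p and D are assumptions. The upper p equals the plan's 15% dropout allowance, and the documents give no value for D.

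| p | D = 1 | D = 3 | D = 5 |
|---|---|---|---|
| 5% | 0.05 (2%) | 0.15 (6%) | 0.25 (9%) |
| 10% | 0.10 (4%) | 0.30 (11%) | 0.50 (19%) |
| 15% | 0.15 (6%) | 0.45 (17%) | 0.75 (28%) |

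Entries are SDRS points, with the share of 2.69 in brackets. At p = 0 the shift is zero.

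**Cross-check with a different model.** Let dropping out have correlation ρ with poor outcome. Then bias = ρ × SD × φ(z_p)/(1 − p), where z_p is the p-quantile and φ the density of the standard normal. With SD 3.00 and p = 15%, this gives 0 at ρ = 0, 0.41 at ρ = 0.5 and 0.82 at ρ = 1. The last two imply D = 0.41/0.15 = 2.7 and 0.82/0.15 = 5.5, so D = 5 at 15% excluded is close to the extreme case.

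A simulation with no true effect (20,000 replicates, 4 of 30 removed from the EA arm only) gave a type I error for one EA-versus-control t-test of 5.1%, 7.5% and 16.9% at ρ = 0, 0.5 and 1.

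**The case against.** The strongest reply is that the text compresses two ordinary analysis sets into two sentences: a per-protocol or modified set, then intention to treat. The first sentence says who is included and does not say only those patients. The second comes last and covers every dropout. The commitment to complete evaluations after dropout fits an intention-to-treat aim. That reading is plausible, and a plan to discard patients should not be inferred. But the article fixes both rules without ranking them, and this reading still leaves the exposure set undefined for controls.

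A reader might infer several stronger points that the documents do not support:

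- *That the rule drops EA non-responders.* It affects those who stop by half-course. A non-responder who attends six or more of the ten sessions stays in. The reference to ineffective treatment sits in a sentence about follow-on care, and nothing says such patients leave by mid-course.
- *That the rule has no possible application to the waitlist arm.* Controls do later receive two courses, so it could be applied, though only through exposure after their assessment.
- *That EA will be favoured.* This needs the rule to be waived for controls and early stoppers to improve less. The second is plausible, but no data are given.
- *That the combined-point versus single-point contrasts are distorted.* This needs early stopping to differ between EA arms, on which the documents are silent.

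The size is also weakly anchored. A D of 3–5 points exceeds the whole planned effect and is 1.0–1.7 planned SDs. The 15% allowance covers dropout at any time, not only by half-course. The Trial status section reports that all 115 recruited so far completed the intervention. At face value, p has been zero to date. These objections limit the magnitude but do not reconcile the two sentences.

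**Conclusion.** The point holds as a defect in a stated rule. The protocol gives two inclusion rules, does not say which is primary, and they conflict for any EA patient who stops at or before half the course. The exposure rule selects on treatment after randomisation and cannot be applied evenly to a control arm untreated at its assessment.

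The consequence is possible bias in EA versus control, of unknown size. The illustrative range of 0.05–0.75 SDRS points (2–28% of 2.69) rests on assumed values of p and D and on the rule being waived for controls. If every patient completes, both rules give the same EA arms and the shift is nil. The reported 115 of 115 points that way, but recruitment was still open, and the article does not give that count by arm or say whether it covers everyone randomised. The documents do not show that any result has been or will be biased.

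**What to change.** - **Primary set.** Keep the intention-to-treat sentence and add that the primary analysis includes all randomised patients in the arm assigned, regardless of sessions received, using the end-of-week-2 SDRS, which is sought from those who stop early.
- **Exposure set.** Relabel the more-than-half rule as a secondary sensitivity set and give its threshold as a number of sessions. State that it restricts the EA arms only, that controls are retained if they completed the waiting-period assessment, and that this comparison is not protected by randomisation. An EA-only restriction keeps the asymmetry described above, so the caveat must accompany the result.
- **Accounting.** Report all randomised patients by arm, counted from the envelopes opened, alongside the 115 recruited and completed.

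The cost is a few sentences. Follow-up of dropouts to complete evaluations is already planned, so no new procedure is needed. The downside is that the estimate may become slightly less favourable to EA. If nobody stopped early, it does not change.
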